## Abstract

**Background:**

Sexual- and gendered harassment are normalised in many peer groups, yet their associations with mental health concerns among adolescents are well-established. School based interventions that prevent and reduce sexual and gendered harassment among younger adolescents are scarce. For schools, protecting pupils from harassment may be challenging if the behaviour is trivialised among the pupils themselves. In the current study, the school intervention “Stop Sexual Harassment” was therefore developed to help teachers and pupils detect, address and stop sexual and gendered harassment among pupils ages 13–15 in Norwegian secondary schools.

**Methods:**

In this study the effectiveness of “Stop Sexual Harassment” is evaluated *via* a cluster randomised controlled trial among pupils and teachers at 38 secondary schools. Schools were randomised into intervention and control groups. Primary outcomes are sexual and gendered harassment victimisation and perpetration, which will be assessed by the administration of questionnaires to pupils and teachers at baseline, and 2-, and 7-months follow-up. A process evaluation of the intervention implementation will be conducted through focus group interviews with pupils and teachers to gain insight about their experiences with the program components and implementation of the intervention.

**Discussion:**

If the intervention yields positive effects, large-scale implementation of the program may be offered for secondary schools. The program may thus reduce sexual and gendered harassment among young adolescents.

**Clinical trial registration:**

clinicaltrial.gov; identifier: NCT04716400.

## 1. Introduction

In the Nordic countries, sexual and gendered harassment are relatively common among lower secondary school pupils (12–15 years of age) (1–3). This is particularly the case for sexual minority pupils (e.g., lesbian, gay, bisexual, queer, etc.) (4–6). In this study, sexual harassment is defined as unwanted sexual attention that may be physical, verbal and non-verbal. Gendered harassment is defined as harassment based on gender identity, gender expression and sexual orientation. The associations between exposure to sexual and gendered harassment and mental health problems among adolescents are well-established. Longitudinal studies support that sexual and gendered harassment lead to depressive symptoms (4–6) as well as emotional distress (5, 7). Furthermore, being exposed to sexual or gendered harassment is associated with higher levels of suicidal feelings among young people (8, 9). In Norway, schools are obliged by law to protect pupils from being exposed to harassment (10), including sexual and gendered harassment (11, 12). Even though sexual and gendered harassment is significant concerns to adolescents' mental health, and is illegal by Norwegian law, there are few resources or programs available to schools to help prevent or intervene against it (13).

While there has been an increasing focus on how to reduce and prevent dating violence (violence or threats of violence within a dating relationship which may be physical, emotional or sexual) and sexual assaults (intentional sexual contact without consent) in the last decade (14–17), only a few interventions address sexual harassment among secondary school pupils under 16 years of age. The school-based interventions “Dating Matters,” “Green Dot” and to some extent “Shifting Boundaries” have been found to reduce sexual harassment in this age group (18–20). However, a major focus of these programs is to reduce sexual harassment or violence within dating relationships. While some pupils perceive sexual harassment as a part of “natural” heterosexual dating (21–24), sexual harassment also occurs outside of a dating relationship and is normalised among some adolescents (22, 25–28). Intervention programs should thus put a greater focus on sexual harassment among non-dating peers in schools. Also, as some pupils seem to perceive sexual harassment as playful and harmless (22, 27, 29) there is a need for interventions which help pupils identify “normalised” unwanted sexual attention as sexual harassment.

There is limited knowledge concerning what works in preventing gendered harassment. The intervention “Green Dot,” which has been found to reduce sexual harassment perpetration and victimisation (18), only seems to reduce harassment among sexual majority youth, but not among sexual *minority* youth (26). Even though there are several toolkits and campaigns designed to address harassment based on gender, gender expression or sexual orientation, few have been systematically evaluated for effectiveness and reported in the peer-reviewed literature. Of those interventions that have been evaluated, their effectiveness remains uncertain because most evaluations have lacked an experimental design with a control group (30). Thus, there is a need for more knowledge concerning what works in preventing gendered harassment in the school setting.

### 1.1. Aims and hypotheses

The aim of the current cluster Randomised Controlled Trial (RCT) is to evaluate and test the effectiveness of the intervention “Stop Sexual Harassment” in Norwegian schools. The following hypotheses are posed:

- Schools participating in “Stop Sexual Harassment” will reduce sexual and gendered harassment victimisation and perpetration among pupils compared to schools in a wait-list control condition.- Schools participating in “Stop Sexual Harassment” will increase pupils' prosocial bystander behaviour when a co-pupil is exposed to sexual and gendered harassment compared to schools in the wait-list control condition.- Schools participating in “Stop Sexual Harassment” will increase teachers' awareness of, and interventions towards sexual and gendered harassment among pupils compared to teachers in the wait-list control condition.- Schools participating in “Stop Sexual Harassment” will increase pupils' attitudes, norms, behavioural control, and willingness to intervene when a co-pupil is exposed to sexual and gendered harassment compared to schools in the wait-list conditions.

Process evaluation of the intervention implementation will be conducted to provide insight into the delivery, quality, and engagement with program components, in order to understand facilitators and barriers to the successful implementation of the intervention and indicate some explanations regarding *why* the intervention does or does not have an effect. This will provide useful data to make further adaption to the intervention for acceptability and effectiveness if the intervention is to be scaled up (31).

## 2. Methods and analysis: Randomised controlled trial

### 2.1. Intervention

“Stop Sexual Harassment” aims to prevent sexual and gendered harassment among pupils in secondary school, which in Norway involves pupils 13–15 years of age in 8–10^th^ grade. The intervention is delivered as eight structured lessons for pupils, administered by their class teacher at school, and during school hours. The training for teachers and other staff includes participation in a digital course comprising the same topics as the pupil lessons. For information about the steps, time frame and duration of the delivery of “Stop Sexual Harassment,” see Table 1. Each structured lesson consists of an illustrated teacher-led digital lecture that come with individual-, group- and class- assignments and discussions. Each lesson is described thoroughly in manuals for teachers on how to lead and conduct the assignments and discussions.

**Table 1 T1:** Delivery of “Stop Sexual Harassment.”

	**First month of a new school year**	**First 4 month of a new school year**	**From the start of the school year and onging**
Class teachers	Individual participation in a digital course comprising eight lectures and preparation of eight pupil lectures with the same topic. This can be done in 1 day, or over several days during the course of August (Duration: 7 h pluss time for practical preparations prior to each lecture).	Delivery of eight structured lessons to pupils in class. (Duration: 8 lessons X 60 min).	Teachers intervene when sexual and gendered harassment is detected.
Other school staff (including school administration, teachers and assistants)	Individual participation in a digital Course comprising four lectures (Duration: 2–3 h).		Staff intervene when sexual and gendered harassment is detected.
Pupils		Participation in eight structured lessons during school hours (Duration: 8 lessons X 60 min).	Pupils tell a teacher when observing or being exposed to sexual and gendered harassment. When safe; pupils show disapproval when a co-student exposes another pupil to sexual and gendered harassment, or when they are exposed to this themselves.

The program is tailored to help teachers and pupils *detect* gendered and sexual harassment, as well as to train them to *address and stop* the harassment. The eight lectures follow Latane and Darley's classical five-step model that leads to intervention in an emergency (32). See Table 2 for an overview of the content, aims and assumed change mechanisms for the intervention. Applying Latane and Darley's (32) model to the prevention of gendered and sexual harassment, the pupils need to (1) Detect unwanted and harmful behaviours that constitute gendered and sexual harassment, (2) Realise that the harassment needs to stop, (3) Be prepared to tell their teachers about the harassment, (who in turn intervene against the harassment), (4) Obtain *skills* regarding how to signal disapproval when someone (a co-student, or they themselves) are harassed, and finally (5) When safe, signal disapproval when witnessing or being exposed to sexual and gendered harassment. The assumed change mechanisms of the program theory are drawn from the Theory of Planned Behaviour. This theory states that an individual's behaviour can be predicted by their behavioural intentions. These intentions are determined by the following three factors: (a) attitudes towards the behaviour (e.g., the extent to which an individual approves or disapproves of the behaviour); (b) subjective norms (e.g., the extent to which an individual perceives others to approve or disapprove of the behaviour or how to respond to it); and (c) perceived behavioural control (e.g., the extent to which an individual have the skills to or feels capable of acting) (33). In line with this theory, the program aims to influence attitudes, norms and perceived behavioural control when it comes to signaling disapproval and/or telling a teacher when a co-pupil harasses another pupil, or if pupils are exposed themselves. The program theory of “Stop Sexual Harassment” also builds on bullying prevention research (34–37) and bystander psychology (38–40).

**Table 2 T2:** The content, aims, and assumed change mechanism for “Stop Sexual Harassment” intervention.

**Latane and Darley (32) five step model that leads to intervention in an emergency**	**Lessons**	**Aim of class activities**	**Assumed change mechanism**
	Lesson 1: Prevention of sexual and gendered harassment.	To create a safe space for future lectures	
Step 1: Noticing the event.	Lesson 2: Detecting sexual harassment.	To become aware that sexualized attention is unwanted for many pupils.	KNOWLEDGE: More pupils will recognise sexual harassment behaviour. NORMS: More pupils will challenge the view that sexual harassment is “normal adolescent behavior.”
Step 1: Noticing the event.	Lesson 3: Detecting gendered harassment.	To become aware how gendered harassment is manifested and how it harms sexual minorities, and anyone who violates traditional gender normative behaviour.	KNOWLEDGE: More pupils will recgonize gendered harassment behaviour. NORMS: More pupils will challenge the view that gendered harassment is “normal adolescent behaviour.”
Step 2: Interpreting the event as an emergency that requires help.	Lesson 4: Sexual and gendered harassment in our school.	To identify behaviour characterised as sexual and gendered harassment in their school which needs to stop.	ATTITUDES: More pupils will perceive harassment behaviour as problematic, which calls for action.
Step 3: Accepting responsibility for intervening.	Lesson 5: The teachers' responsibility.	To practise telling a teacher when a co-student is exposed to harassment.	ATTITUDES: More pupils will believe it is ok to tell their teacher if a co-pupil or they themselves have been exposed to harassment.
	Lesson 6: Knowing what is illegal	To explore what behaviour is characterise as sexual assaults by Norwegian law.	
Step 4: Knowing how to intervene or providing help.	Lesson 7: Our responsibility as a co-student.	To practise how to signal disapproval when a co-pupil harasses another pupil.	ATTITUDES: More pupils will believe it is ok to signal disproval when a co-student harasses another pupil. NORMS: More pupils will believe their co-pupils will support them if they signal disapproval when a co-pupil harasses another pupil. CONTROL: More pupils will have the skills to signal disproval when a co-student is exposed to harassment.
Step 4: Knowing how to intervene or providing help.	Lesson 8: What we can do ourselves.	To be able to use the disapproval statements for future harassment victimization.	CONTROL: More pupils will have the skills to signal disproval when they are exposed to sexual harassment themselves.
Stop 5: Intervene in the situation	After completing all lectures.	To signal disapproval or tell a teacher when a co-pupil or the pupils themselves are exposed to harassment.	INTENTIONS:- More pupils will intend to signal disproval when a co-student harasses another pupil or if they are harassed themselves. - More pupils will intend to tell their teacher if a co-pupil or they themselves are exposed to harassment. BEHAVIOUR: - Fewer pupils will engage in harassment perpetration. -Fewer pupils will experience harassment victimisation. - More pupils will tell their teacher if a co-pupil or they themselves are exposed to harassment. - More pupils will signal disapproval when a co-student harasses another pupil, or if they are harassed themselves.

### 2.2. Study design

This study uses a cluster randomised controlled superiority trial with two parallel groups of schools; one intervention group and one delayed access wait-list control group. The schools in the wait list condition will receive the intervention after the data are collected. The study will thus utilise quantitative data to assess the effect of the intervention.

### 2.3. Sample size and power

Multilevel modelling will be used to analyze the effect of the intervention on sexual and gendered harassment victimisation and perpetration. By taking this approach, we will take into account the hierarchical design of the data due to cluster randomisation by school and school class. In Norway, secondary school pupils are in the same class, with the same peers all week except for a few hours. We approximated cluster effects (Intra Class Correlation; ICC) that may influence the main outcomes (sexual and gendered harassment and emotional problems) by taking advantage of results from previous studies. Previous studies indicate that the school and/or school class level contribute to relatively little (<5%) of the total variance of sexual harassment victimisation, bullying and emotional concerns. However, some studies suggest that this might not be the case for attitudes towards sexual minorities, where between 12.5 and 30% of the total variance has been explained by school/ class levels. Power calculations, applying the Optimal Design Software, show that 38 schools are needed to detect effect sizes of 0.30 (small to medium effects), according to Cohen (41). This is based on a 0.05 level of significance, power = 0.80, ICC level 2 = 0.25, IC level 3 = 0.05, number of cluster level 2 = 6 (classes), and a cluster size=20 (pupils). The statistical power of the analyses can be increased by including the pre-intervention measure of the outcome variables as a covariate. Assuming that the average school level of the outcome variable at pre-intervention explains 50 or 30 percent of the variation of the outcome variable at *post-test*, this decreases the number of schools to 30 and 32, respectively, given the same assumptions as above. We therefore decided to include at least 32 schools (16 intervention schools) to guard against the possibility of Type II errors. Thus, a minimum of 3,840 pupils (32 schools × 120 students) should take part in the study to have sufficient statistical power.

### 2.4. Recruitment

Schools were recruited to take part in the “Stop Sexual Harassment” intervention and the randomised control trial (RCT) at two time points. The recruitment of schools started in March 2019 and ended in May 2022. In the first recruitment phase, schools in the counties of Rogaland, Vestland, Nordland and Buskerud/Viken were invited to participate during autumn 2021. In the second recruitment phase, more schools in these counties, in addition to schools in the cities of Oslo and Trondheim were invited to participate during autumn 2022. Two recruitment phases were needed because several schools in wave 1 withdrew from the study due to the schools' management of the COVID-19 pandemic and its regulations. Please see Figure 1 for a flow chart of the participation rate. In the end, all secondary schools in Norway were made eligible for participation. Schools were invited by postal mail and/or e-mail and follow-up phone calls or by regional and national news channels/newspapers.

**Figure 1 F1:**
[figure not shown]
Flow diagram for study participants.

Inclusion criteria were public and private upper secondary schools in Norway. Exclusion criteria were schools where the curriculum is taught in languages other than Norwegian, and schools for pupils with disabilities or other health impairments (e.g., hospital schools). In Norway, upper secondary school consist of grade 8–10. All school staff within the intervention schools are encouraged to complete the digital training for “Stop Sexual Harassment” and to deliver the structured lessons to their pupils, regardless of whether or not they agree to take part in the RCT study (i.e., by participating in data collection through completing a survey). Pupils within the participating classes are not granted the opportunity to opt out of participating in the lessons, even if they do not consent to participate in the RCT. As such, all pupils will be exposed to the materials, as the intervention is delivered to the class as a whole, but youth who do not consent to participate in the RCT will not complete any surveys.

All teachers and pupils in 8th and 9th grade (during the time of recruitment) at the participating schools are invited to take part in the RCT. Participation involves completing three questionnaires at three time points. At each school, pupil questionnaires are administered by class teachers who follow written instructions from the principal investigator. Prior to participation, the child's class teachers provide parents with consent forms including information about the study. Parents, pupils, and teachers are informed in their respective consent form that it is voluntary to participate and that they have the right to withdraw from the study at any point in time. This information is repeated orally for pupils prior to completing the questionnaires during school hours. Pupils who do not want to participate in the study are given other assignments prepared by their class teachers during the time allocated for completing the questionnaires.

### 2.5. Randomisation procedure

The intervention “Stop Sexual Harassment” is a whole school approach that involves all members of the school community. Comparisons must thus be at the school and not the individual level and schools were chosen as the cluster of randomisation. Schools were randomised into intervention and control schools by an independent professional [i.e., external statistician working at Services for sensitive data (TSD)]. The randomisation was stratified based on number of participating classes within each school with a 1:1 allocation. All schools were paired based on similarity in size of participating classes and whether they were public or private schools. Syntax (in stata) was used to randomly assign one school in each pair to the intervention group for both wave 1 and wave 2. The remaining school of each pair was assigned to the wait-list control group. Schools were informed about their allocation after completing baseline questionnaires.

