### 2.6. Baseline and follow-up assessments

Pupils and teachers will complete separate baseline questionnaires, and two follow-up questionnaires spaced at 2- and 7- months post-intervention. By comparing baseline and follow-up questionnaires between the intervention schools and the control school, we will be able to assess whether the intervention “Stop sexual harassment” is successful in reducing sexual and gendered harassment victimisation and perpetration among pupils. See Table 3 for a timeline of the intervention and the assessments, and Figure 1 for a flowchart of the participation rate. The primary outcomes variable consists of instruments that measure sexual harassment (28, 42) and harassment due to gender non-conformity, sexual harassment and homophobic behaviour (43, 44). For a description of primary, secondary and mediator variables, see Tables 4–6.

**Table 3 T3:** Timeline of the intervention and the assessments.

	**Wave 1**	**Wave 2**
Baseline Assessment (T1)	May–June 2021	May–June 2022
Randomisation	June 2021	June 2022
Training of teachers	August 2021	August 2022
Implementation of “Stop Sexual Harassment”	August 2021–November 2021	August 2022–November 2022
Focus group interviews		December 2022
Short term follow-up (T2)	January- March 2021 (Delay due to the COVID-19 Pandemic)	January 2023
Long term follow-up (T3)	June 2022	June 2023

**Table 4 T4:** Primary outcome variables.

	**Measure**	**Source of measure**	**Data source**
Sexual harassment *victimisation*	The AAUW sexual harassment survey (13 items)	AAUW (42); Hill and Kearl (28)	Pupils
Harassment *victimisation* due to gender non-conformity	Modified version of the Harassment perceived as occurring due to gender non-conformity (4 items)	Based on Martin-Storey and August (43)	Pupils
Harassment *victimisation* due to sexual orientation	Modified version of the Harassment perceived as occurring due to sexual minority status (4 items)	Based on Martin-Storey and August (43)	Pupils
Sexual harassment *perpetration*	The AAUW sexual harassment survey (13 items)	AAUW (42); Hill and Kearl (28)	Pupils
Harassment *perpetration* due to gender non-conformity	Modified version of the Harassment perceived as occurring due to gender non-conformity (4 items)	Based on Martin-Storey and August (43)	Pupils
Harassment *perpetration* due to sexual orientation	Modified version of the Harassment perceived as occurring due to sexual minority status (4 items)	Based on Martin-Storey and August (43)	Pupils

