### 2.8. Data analysis

Descriptive statistical analyses and frequency tables will be used for comparisons between intervention and control group. Multilevel modelling will be used to assess the impact of the intervention on the primary and secondary outcome variables. Potential subgroup differences (e.g., gender) will be analysed by including interaction effects. The psychometric qualities of the outcome variables will be assessed by descriptive statistics (e.g., floor/ceiling effects), correlation analyses and exploratory and confirmatory factor analysis. Missing data will be handled by multiple imputation and full information maximum likelihood.

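### Schools were paired and randomised within pair in each wave, but the analysis text names only school and class clustering; adjusting for wave, class number and school type would recover modest power at almost no cost

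*Protocol article*

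**What the plan says.** **Allocation (protocol article, 2.5).** "All schools were paired based on similarity in size of participating classes and whether they were public or private schools". Within pairs, "Syntax (in stata) was used to randomly assign one school in each pair to the intervention group for both wave 1 and wave 2"; the other school of each pair went to the wait list. The same section also says: "The randomisation was stratified based on number of participating classes within each school with a 1:1 allocation". I read the size criterion in the pairing sentence as this number of participating classes. Table 3 (in 2.6) dates the randomisation of the two waves a year apart, in June 2021 and June 2022.

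**Analysis (2.3 and 2.8).** Section 2.8 gives the effect model one sentence: "Multilevel modelling will be used to assess the impact of the intervention on the primary and secondary outcome variables". It then adds subgroup interactions and missing-data methods. Section 2.3 says which design feature the model handles: "we will take into account the hierarchical design of the data due to cluster randomisation by school and school class". The only covariate mentioned is the pre-intervention outcome, as something that can raise power. Pair, class number, school type and wave appear nowhere as model terms, and nowhere are they said to be left out.

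**Sample size (2.3).** "38 schools are needed to detect effect sizes of 0.30", on the basis of a "0.05 level of significance, power = 0.80, ICC level 2 = 0.25, IC level 3 = 0.05", with 6 classes per school and 20 pupils per class. No matching parameter enters.

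**The concern.** Pairing within wave balances number of classes, school type and wave between the arms. Outcome variation due to those factors therefore drops out of the arm contrast. A model without them still counts that variation as residual school-level error. Its standard error is then larger than the true sampling error of the contrast, its confidence intervals are too wide, and its test runs below the nominal 5%. The trial would have gone to the trouble of matching without collecting the benefit.

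There is a second, smaller stake. If the plan does not say how pairs and wave enter the model, someone must choose later, possibly after seeing the data, between pair effects, covariates or neither.

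**Working it through.** **Inputs.** From 2.3: school ICC 0.05, class ICC 0.25, 6 classes, 20 pupils, effect 0.30 SD, alpha 0.05 (sidedness not stated; two-sided assumed). From 2.5: pairs, 1:1. Not in the documents: the share R of school-level variance explained by the matching factors and wave. I use R = 0, 0.10, 0.20 and 0.30 as an assumed range.

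**Step 1: reproduce the 38 schools.** The variance of a school mean is V = 0.05 + 0.25/6 + 0.70/120 = 0.0500 + 0.0417 + 0.0058 = 0.0975. The standard error of the arm difference with K schools is √(4V/K). At K = 38 it is √(0.390/38) = 0.1013, so the noncentrality is 0.30/0.1013 = 2.96. A noncentral t with K − 2 = 36 degrees of freedom gives 82.2% power. The smallest K reaching 80% is 37, or 38 when rounded to an even number. The stated figure reproduces, and it is that of an unmatched design.

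**Step 2: what matching can remove.** Only the school-level part (0.05) can be shared within a pair, so the pair correlation of school means is r = R × 0.05/0.0975, at most 0.51. The true variance behind the contrast is V(1 − r). The unadjusted model estimates about V, so its standard error is too large by a factor of 1/√(1 − r).

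**Step 3: results at 38 schools (19 pairs).** Type I error and unadjusted power come from simulating normally distributed school means, analysed with an ordinary two-sample t test (36 df). The other two power columns use the noncentral t with variance V(1 − r): 33 df for three added covariates, 18 df for a paired analysis.

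| R | r | SE too large by | Type I error, unadjusted | Power, unadjusted | Power, three covariates | Power, paired |
|---|---|---|---|---|---|---|
| 0 | 0 | 0% | 5.0% | 82.2% | 82.0% | 80.0% |
| 0.10 | 0.051 | 3% | 4.4% | 83% | 84% | 82% |
| 0.20 | 0.103 | 6% | 4.0% | 83% | 86% | 84% |
| 0.30 | 0.154 | 9% | 3.4% | 84% | 88% | 86% |

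(The 82.2% and 5.0% at R = 0 are the exact values.)

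**Step 4: covariates or pair effects.** Pair effects halve the degrees of freedom, from 36 to 18. On confidence-interval width they beat the unadjusted analysis only when r exceeds about 0.07, which is R of about 0.13. With fixed pair effects, a school whose pair-mate has withdrawn contributes nothing. If four of the 38 schools were lost from four different pairs, 15 pairs would remain. At R = 0.20, paired power is then about 73%, against about 78% for an unadjusted analysis of the 34 remaining schools. Section 2.4 reports withdrawals in wave 1.

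**Step 5: after baseline adjustment.** Suppose the baseline outcome removes 30% of the school-level variance, one of the two values in 2.3. Then 0.035 remains and V = 0.0825. If the factors explain 10, 20 or 30% of that remainder, r = 0.0035, 0.0070 or 0.0105 divided by 0.0825, and the standard errors are about 2, 5 or 7% too large. The share itself may also fall, because the baseline outcome can absorb stable differences by size, school type or wave.

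**The case against.** The strongest objection is that the omission is read from silence. This is a condensed article, no list of model terms is given, and covariates for matching factors are commonly set out in an analysis plan that is not shown here. A reader might infer that the trial will ignore pairing and wave; the documents do not establish that. What remains is that 2.3 does describe the design feature the model is to handle. It names clustering by school and class, does not mention the pairs and waves of 2.5, and sizes the trial as unmatched. Followed as written, that is the model examined above.

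Second, the harm is conditional. If number of classes, school type and wave do not predict harassment outcomes, nothing is lost by leaving them out. This stands.

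Third, larger losses can be produced by assuming that the factors explain 10 to 40% of the variance of school means. At 40%, type I error falls to about 1.4%, and power is about 88% unadjusted against 95% paired. But 40% of 0.0975 is 0.039, which is 78% of the school-level variance of 0.05, and the 95% belongs to a paired t test, not to the covariate model. The stated ICCs do not make that a realistic working case.

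Fourth, a reader might infer that wave is the dominant factor because COVID-19 disrupted wave 1. The documents tie the disruption to wave 1, but they do not say that wave 2 was free of restrictions and give no effect of wave on any outcome.

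**Conclusion.** The point holds as a modest matter of precision. The allocation in 2.5 is restricted by pair and wave, and the analysis and sample-size text in 2.3 and 2.8 does not reflect this. If the factors explain 10 to 30% of school-level variance, the unadjusted model overstates standard errors by 3 to 9% and gives up roughly 1 to 4 points of power at 38 schools. Baseline adjustment makes the gain smaller.

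Any error is conservative. The arm contrast is not biased, type I error stays at or below 5%, and unadjusted power at 38 schools remains about 82% or more under the stated inputs. It would be wrong to conclude that the trial's validity is at risk. The figures rest on the ICCs and cluster sizes in 2.3, a two-sided test, complete pairs and the assumed range of R.

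**What to change.** State in 2.8, or in the analysis plan before outcome data are compared by arm, that every outcome model includes wave, number of participating classes and public/private status as fixed school-level covariates, alongside the baseline outcome, with school-level degrees of freedom reduced accordingly. Report a pair-level analysis as sensitivity only, for the reasons in step 4; the covariates keep a school whose pair-mate withdrew.

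In the same edit, clarify in 2.5 how the stratification by class number relates to the pairing, and correct the phrase in 2.3 that reads as if classes were randomised as well as schools.

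The cost is wording and about three school-level degrees of freedom, or 0.2 points of power at 38 schools if the factors explain nothing.
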